**Aim #1:**

Detection of mutations in untreated subjects over time

**Figure 5:** Baseline HIV-1 drug resistance testing will be performed using OLA and consensus sequencing on the first available specimens from subjects with acute and very early HIV-1 infection who enroll in the PIC cohort and from subjects previously enrolled in the cohort who meet eligibility criteria for study. ARV-naïve subjects with mutations detected at baseline will provide specimens to determine the detection of mutations over time (**Aim #1**). Subjects both with and without HIV-1 drug resistance at baseline who initiate ARV therapy during follow-up will provide specimens to determine whether increased levels of HIV-1 drug resistance mutations are detected in PBMCs during ARV therapy and whether low-frequency mutations impact the response to ARV therapy (**Aim #2**). Subjects enrolled in the PIC Cohort study will refer potential source partners to the PIC Partners study. Partners will be asked to provide blood and genital specimens in order to compare patterns of HIV-1 drug resistance within transmission pairs (**Aim #3**).

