**Aim #2: Quantify the increase in detection of low-frequency mutations in PBMCs during ARV therapy.**

Primary objectives:

1) Compare the proportion of subjects with transmitted HIV-1 drug resistance that have new HIV-1 drug resistance mutations detected in PBMCs 6 and 12 months after the start of ARV therapy compared to subjects without transmitted HIV-1 drug resistance at baseline.

2) Evaluate time to virologic suppression in subjects with transmitted HIV-1 drug resistance compared to subjects without transmitted HIV-1 drug resistance.

Secondary objectives:

1) Explore whether the timing of ARV therapy impacts the increased detection of low-frequency mutations, time to virologic suppression, or time to virologic failure.

2) Explore whether specific mutations (e.g. M184V) are selected for by ARV therapy and are found at a greater level over time within treated subjects with and without HIV-1 drug resistance at baseline.

3) Explore whether specific HIV-1 drug resistance mutations are associated with significant differences in time to virologic suppression and time to virologic failure compared to subjects without transmitted HIV-1 drug resistance.

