**5.c.2 Aim #2: Quantify the increase in detection of low-frequency mutations in PBMCs during ARV therapy.**

The primary objectives of the study described in this aim will evaluate changes in the detection of low-frequency mutations in PBMCs over time during ARV therapy and the virologic consequences of ARV therapy in the setting of transmitted low-frequency HIV-1 drug resistance. We hypothesize that, over time, additional mutations will be detected in a greater proportion of treated subjects with transmitted drug resistance compared to treated subjects without HIV-1 drug resistance detected at baseline, because the relative level to which viral replication is suppressed will be diminished in the former group. Secondary analyses will explore associations between specific HIV-1 drug resistance mutations, the interval between HIV-1 acquisition and the start of ARV therapy, the increased detection of HIV-1 drug resistance mutations, and treatment outcomes including time to virologic suppression and time to virologic failure.

This longitudinal study will evaluate subjects enrolled in the PIC cohort within 30 days of the estimated date of HIV-1 infection, who initiate ARV therapy at any point following the baseline evaluation, and who achieve undetectable HIV-1 RNA levels (less than 50 copies/mL) within six months after the start of ARV therapy. OLA will be performed using PBMCs collected at the visit immediately prior to the start of ARV therapy (unless this visit is within 4 weeks from the baseline specimen) and in specimens obtained 6 and 12 months following the start of treatment. The detection of a new mutation will be defined as any mutation detected during follow-up that was never previously detected. Additional analyses will use the semi-quantitative nature of OLA to evaluate the changes in levels of mutations during ARV treatment (i.e. <5%, 5-10%, 10-30%, 30-50% >50% of the viral quasi-species) and the reappearance of mutations that had been detected at baseline but were lost to detection prior to the start of ARV therapy in the absence of ARV selection pressures.

**Table 9: Sample size needed in each arm to detect a difference in proportion of subjects with new low-frequency mutations**

|  | | Percent of subjects with low-frequency mutations at baseline who have new mutations detected after start of ARVs | | | |
| --- | --- | --- | --- | --- | --- |
| 20% | 30% | 40% | 50% |

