**Table 10: Precision estimates for proportions of subjects with new drug resistance mutations detected**

| Sample size | 10 | 20 | 30 | 40 | 50 | 100 |
| --- | --- | --- | --- | --- | --- | --- |
| 95% confidence interval (+/-) | .31 | .23 | .19 | .16 | .14 | .10 |

With the increased study size compared to the pilot project, we will perform a definitive analysis to assess the impact of low-frequency mutations on time to virologic suppression (defined as HIV-1 RNA less than 50 copies/mL). Survival analyses will evaluate the time to virologic suppression among subjects with transmitted low-frequency HIV-1 drug resistance mutations detected who are on ARV regimens with fewer than three active agents compared to subjects without transmitted HIV-1 drug resistance, controlling for the baseline HIV-1 RNA level. If a significant difference is detected, we will use additional Cox proportional hazard models to explore characteristics (e.g. HLA type, specific mutation or class of ARV therapy, and timing of ARV treatment) that might impact time to virologic suppression.

We will also perform a survival analysis evaluating the time to virologic failure among subjects with transmitted low-frequency HIV-1 drug resistance mutations who are on ARV regimens with fewer than three active ARV agents compared to subjects without transmitted HIV-1 drug resistance, controlling for baseline HIV-1 RNA level and the timing of initiation of ARV therapy. For purposes of this analysis, virologic failure will be defined as any one of the following:

1) Failure to suppress viral replication (HIV-1 RNA greater than 400 copies/mL after 24 weeks or greater than 50 copies/mL on two occasions after 48 weeks)

2) Addition or substitution of ARVs because of delay in viral suppression

3) Detectable HIV-1 RNA (greater than 400 copies/mL) on two consecutive occasions following viral suppression

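### Aim 2's only eligibility rule requires suppression within six months, yet time to suppression is a primary outcome and no other population is defined for it

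*Protocol*

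**What the plan says.** Section 5.b gives Aim 2 two primary objectives. The first compares the proportions with new mutations in PBMCs 6 and 12 months after ARV start. The second is: "Evaluate time to virologic suppression in subjects with transmitted HIV-1 drug resistance compared to subjects without transmitted HIV-1 drug resistance". Time to virologic failure appears only among the secondary objectives.

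Section 5.c.2 introduces both primary objectives and then gives one eligibility statement: enrolled within 30 days of the estimated infection date, starting ARV therapy at any point after baseline, "and who achieve undetectable HIV-1 RNA levels (less than 50 copies/mL) within six months after the start of ARV therapy".

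Later in 5.c.2, after Table 10, the second objective is specified: "With the increased study size compared to the pilot project, we will perform a definitive analysis to assess the impact of low-frequency mutations". The event is "time to virologic suppression (defined as HIV-1 RNA less than 50 copies/mL"), the threshold used in the eligibility rule. The failure analysis follows. Its first criterion opens "Failure to suppress viral replication (HIV-1 RNA greater than 400 copies/mL after 24 weeks" and has a second limb, RNA above 50 copies/mL on two occasions after 48 weeks. Its second is "Addition or substitution of ARVs because of delay in viral suppression". Its third is two consecutive values above 400 copies/mL after suppression.

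The survival paragraphs name comparison groups (low-frequency mutations with fewer than three active agents, against no transmitted resistance) but no analysis population. The Figure 5 legend in 5.a describes the Aim 2 subjects as those with and without baseline resistance "who initiate ARV therapy during follow-up will provide specimens to determine whether increased levels of HIV-1 drug resistance mutations are detected in PBMCs", with no suppression condition.

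**The concern.** The eligibility rule is the outcome of primary objective 2, observed early. Anyone who meets it has had the suppression event by month six, and anyone who has not cannot enter. Resistance is the exposure and is suspected of slowing suppression, so the rule removes more exposed than unexposed subjects, and those it removes are the slowest. What remains is a comparison of how quickly eventual early suppressors got there, which understates any true difference.

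Section 5.f.4 relies on time to suppression because the failure analysis has limited power, and says that a randomised trial would be designed if an adverse effect is suggested. A result diluted toward 1 could be read as showing that low-frequency resistance does not matter for treatment response.

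**Working it through.** **1. The plan's own figure.** The Aim 2 sample size is 35 without and 18 with baseline mutations (Table 9: 10% v 50%, alpha 0.05, power 80%). Take two-sided alpha, ratio r = 0.5 and difference d = 0.4. The pooled proportion is (0.10 + 0.5 × 0.50)/1.5 = 0.233.

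- Uncorrected: n' = [1.96√(1.5 × 0.233 × 0.767) + 0.842√(0.5 × 0.09 + 0.25)]² / (0.5 × 0.16) = 27.1, rounded up to 28.
- With continuity correction: n = (n'/4)[1 + √(1 + 2 × 1.5/(n' × 0.5 × 0.4))]² = 34.2, rounded up to 35, hence 18 in the other group.

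The figure reproduces and is not in dispute. It was derived for the new-mutation endpoint only.

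**2. Who the rule removes.** Let p0 be the proportion of subjects without resistance who suppress by 26 weeks. The protocol does not give it, so 70-95% is assumed. Under proportional hazards with hazard ratio HR, the proportion of exposed subjects kept is 1 − (1 − p0)^HR. For HR = 0.5:

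- p0 = 0.95: 1 − 0.05^0.5 = 78% kept, against 95% of unexposed.
- p0 = 0.70: 1 − 0.30^0.5 = 45% kept, against 70% of unexposed.

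**3. What happens to the hazard ratio.** Times to suppression were simulated under proportional hazards (exponential and Weibull), only times up to 26 weeks were kept, and a Cox model was fitted. The Cox estimate depends only on the order of the times, so the Weibull shape does not matter in large samples.

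| p0 | True HR 0.5, restricted cohort |
|---|---|
| 0.95 | 0.69 |
| 0.90 | 0.75 |
| 0.80 | 0.81 |
| 0.70 | 0.86 |

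Across repeated runs the range is about 0.68-0.87 for a true 0.5 and about 0.80-0.92 for a true 0.7. Keeping every initiator and censoring at 26 weeks returns the true value (0.50 for 0.5). The bias therefore comes from the exclusion and not from short follow-up.

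**4. Effect on power.** Using 53 events split 18/35, power = Φ(√(53 × 0.34 × 0.66) × |ln HR| − 1.96). At HR 0.5 this is Φ(3.45 × 0.693 − 1.96) = 67%. At 0.75 it is Φ(3.45 × 0.288 − 1.96) = 17%. The planned comparison uses only those with fewer than three active agents, so these figures are generous.

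**5. The failure criteria under the rule.**

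- Criterion 1, as never suppressing or suppressing after six months: excluded. As viraemia after early suppression (above 400 after 24 weeks, or above 50 twice after 48 weeks): still possible.
- Criterion 2: possible only in subjects who still reach below 50 copies/mL by six months.
- Criterion 3 (rebound): fully observable.

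**6. Passages that do not fit the rule.** The Figure 5 legend describes all initiators. Section 5.f.4 describes the failure comparison among subjects who start ARV therapy. Section 5.c.2 claims a larger study than the pilot, but the pilot suppression analysis in 4.g had 14 + 10 + 55 = 79 subjects, and Aim 2 plans 53. The accrual paragraph counts 20 pilot subjects who achieved suppression, then twenty more for whom only six months of treatment is stated.

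**The case against.** The best defence is that the rule was never meant for the survival analyses. It opens the paragraph on PBMC sampling and the definition of a new mutation, and it matches the Specific Aims wording about successful therapy. The survival paragraphs come later and name their own comparison groups. A claim of increased size over the pilot is wrong if the 53 are meant, and a criterion for failing to suppress has little purpose if non-suppressors are out. The pilot analysed treated subjects generally.

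This has weight as evidence of intent, and a reader should not infer that the investigators deliberately chose the restricted cohort. It does not settle the text. The rule is the only population stated, it follows an introduction covering both objectives, and the other passages contradict it without replacing it. Endpoint-specific populations may be left to an SAP, but here the protocol has stated one, and an SAP that followed it would carry the bias forward.

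On size, true hazard ratios of 0.5 or less lie below the pilot's interval for subjects with fewer than three active agents (1.1, 95% CI 0.54-2.3). That is fair. The 0.7 row lies inside it, and the pilot estimate itself would move only from 1.1 to about 1.02-1.06. The illustration also omits the planned adjustment for baseline RNA.

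One might further infer that the rule removes the main failures or makes criterion 1 impossible. The documents do not support that. Criterion 1 has limbs that early suppressors can still meet, rebound is untouched, and 5.c.2 reports four pilot failures without their type. The failure analysis is also secondary and already described as having limited power.

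**Conclusion.** The point holds for primary objective 2. As written, the Aim 2 population is selected on the outcome being analysed, and the hazard ratio is biased toward 1: about 0.68-0.87 for a true 0.5 and about 0.80-0.92 for a true 0.7. These sizes rest on proportional hazards and an assumed 70-95% suppression by 26 weeks in unexposed subjects; the direction does not depend on the exact percentage. For time to failure the consequence is narrower: failures through non-suppression or late suppression are lost, while later viraemia and rebound remain. That the survival analyses use this cohort is inferred from the absence of any other definition. The conflict with the Figure 5 legend, the claim of increased size and section 5.f.4 must be resolved in the text, especially for an analysis the protocol calls definitive.

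**What to change.** In 5.c.2, attach the suppression-within-six-months condition to the new-mutation endpoint (primary objective 1) only. State that time to suppression and time to failure are analysed from ARV start in all ARV initiators with baseline OLA who meet the other Aim 2 criteria, including enrolment within 30 days of infection, whether or not they suppress, with censoring at the last RNA measurement. Bring the Figure 5 legend and 5.f.4 into line. Give the expected size of this set and check the claim of an increase over the pilot against it: the pilot's 79 were not limited to 30-day enrollees, so the claim may not survive.

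The cost is a change of wording. Table 11 schedules HIV-1 RNA at every visit, and 5.c.1 already plans baseline OLA for all selected subjects, so no new assays or visits are needed.

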We propose studies that will use OLA to address questions pertaining to the transmission and subsequent consequences of HIV-1 drug resistance. In **Aim #1**,we will study ARV-naïve PIC subjects to compare the duration of detection ("persistence") and level of detection of transmitted HIV-1 drug resistance over time in peripheral blood mononuclear cells (PBMCs), blood and seminal plasma. In **Aim #2**, we will study PIC subjects initiating ARV therapy and use OLA to determine whether additional mutations can be detected in PBMCs during successful treatment due to the selection of transmitted low-frequency drug resistance mutations or the development of new mutations. In **Aim #3**, we will use OLA to compare HIV-1 drug resistance patterns in PIC subjects and their source partners to determine whether HIV-1 drug resistance impacts "transmission fitness".

These novel investigations would broaden our understanding of the natural history and clinical impact of low-frequency HIV-1 drug resistance and inform guidelines for the testing and treatment of HIV-infected persons. If more-sensitive HIV-1 drug resistance assays were to be endorsed for clinical care before there is a full understanding of the relevance of low-frequency mutations, the potential increase in the complexity of initial ARV regimens and subsequent reduction in patient adherence could paradoxically increase the prevalence of drug resistance. Finally, empiric data from partner-pairs will generate information on correlates of HIV-1 transmission that could be incorporated into future models of the population dynamics of drug resistance. These models would estimate the overall proportion of HIV-1 drug resistance that is transmitted from ARV-naïve source partners with primary HIV-1 infection versus ARV-experienced source partners with established HIV-1 infection. This data could be used to design public health interventions targeted to these populations to reduce the spread of transmitted HIV-1 drug resistance.

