**Aim #2: Quantify the increase in detection of low-frequency mutations in PBMCs during ARV therapy.**

*Rationale:* Transmitted low-frequency mutations have been associated with poor treatment outcomes in some studies [2, 3, 5, 6, 28, 29], but *others have found no association between minority variants and poor response to ARVs* [4]. HIV-1 replicates at low levels in PBMCs during ARV therapy [30, 31], and this may result in the selection or development of HIV-1 drug resistance mutations over time [23, 32-34]. Persons with low-frequency drug resistance who receive ARV therapy may be at greater risk for virologic failure if levels of drug resistance mutations increase in PBMCs at a higher rate than in persons without drug resistance at baseline.

*Methods:* We will use OLA to quantify the proportion of subjects in the PIC cohort who have *new* low-frequency mutations detected in PBMCs after 6 and 12 months of successful ARV therapy. We will examine whether relationships exist between changes in levels of HIV-1 drug resistance and the timing and response to ARVs.

Hypothesis: Over time, additional mutations will be detected in a greater proportion of treated subjects with transmitted drug resistance compared to treated subjects without HIV-1 drug resistance detected at baseline.

Implications: If low-frequency mutations reduce the efficacy of ARV treatment, these data would support the need for clinical trials to evaluate use of more-sensitive assays to select ARVs for drug-naïve persons. Also, if levels of mutations decay prior to the initiation of ARV therapy and do not subsequently reappear during therapy, this would be a *rationale* to defer rather than initiate ARV therapy during primary HIV-1 infection.

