If no difference is identified between groups with and without transmitted HIV-1 drug resistance, an estimate of the proportion of all subjects with primary HIV-1 infection who have new HIV-1 drug resistance mutations detected in PBMCs during ARV therapy would be a novel finding of this study. **Table 10** shows the maximum 95% confidence intervals associated with varying sample sizes used to estimate the proportion of subjects who have new HIV-1 drug resistance mutations detected. If new HIV-1 drug mutations are not detected in any subjects during study follow-up, a sample size of 35 subjects would exclude the possibility that the true proportion of subjects with new mutations detected in PBMCs during virologic suppression is greater than 10%. If we identify significant numbers of subjects who have new HIV-1 drug mutations detected during follow-up, we will use logistic regression analyses to explore whether the detection of additional HIV-1 drug resistance mutations is associated with transmitted HIV-1 drug resistance, the timing of ARV therapy, the HIV-1 RNA level at the start of ARV therapy or rate of the initial viral decay, or treatment adherence.

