**5.f.2 Use of ARV therapy**

The projects proposed in this application will evaluate both treated and untreated subjects with acute HIV-1 infection. If a substantial fraction of untreated enrollees start ARV therapy or treated subjects stop ARV therapy, these subjects will not be able to contribute to the projects as planned. However, our experience suggests that most PIC participants continue with their initial choice or deferral of ARVs. The estimates for numbers and choice of subjects for the prospective studies assume a 10% per year loss to analysis (whether from loss to follow-up or change in ARV status). From an ethical viewpoint, it is important that the pros and cons of ARV therapy for acute HIV-1 infection are presented in an unbiased fashion and allow for use of ARV therapy when indicated (progressive HIV-1 infection or severe CD4+ T-cell depletion).

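### Aim 2 sets no HIV-1 RNA condition at its 6- and 12-month specimens, so mutations first seen after rebound can be described as arising during suppression or successful therapy

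*Protocol*

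**What the plan says.** **Entry and counting rule (5.c.2).** Subjects enrol within 30 days of infection, start ARVs at any later point, and must be among those "who achieve undetectable HIV-1 RNA levels (less than 50 copies/mL) within six months after the start of ARV therapy". OLA is run on PBMCs taken before ARV start and "in specimens obtained 6 and 12 months following the start of treatment". The endpoint is defined without reference to RNA: "The detection of a new mutation will be defined as any mutation detected during follow-up that was never previously detected".

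**How the result is described.**
- The overview at the end of section 1 asks whether "additional mutations can be detected in PBMCs during successful treatment".
- The Aim #2 methods in section 2 speak of new "low-frequency mutations detected in PBMCs after 6 and 12 months of successful ARV therapy".
- The precision paragraph in 5.c.2 says that, with no events, 35 subjects would rule out that the "true proportion of subjects with new mutations detected in PBMCs during virologic suppression is greater than 10" per cent.
- By contrast, the Aim 2 title, primary objective 1 (5.b) and the powered two-group test (5.c.2) refer to ARV therapy or its start, not to suppression.

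**Nearby rules.**
- The virologic failure definition in 5.c.2 includes rebound above 400 copies/mL on two consecutive occasions after suppression, but only as an endpoint of a separate survival analysis.
- Section 5.f.2 says that if "treated subjects stop ARV therapy, these subjects will not be able to contribute to the projects as planned".
- Section 5.f.3 censors at superinfection.

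**The concern.** Reaching RNA below 50 by month 6 does not establish suppression at month 12. Take a subject who suppresses at week 12, rebounds on continued ARVs at week 36 and gives PBMCs at month 12. This subject meets the entry rule, and a mutation first seen in that specimen meets the definition of new.

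The two kinds of finding mean different things. New mutations during viraemia on treatment are unsurprising. New mutations in PBMCs while plasma RNA stays suppressed are what the suppression wording claims. Section 3.d also suggests that PBMC resistance testing might be used for monitoring if new mutations are associated with later failure. If mutations first seen after rebound are in the count, that association becomes partly circular.

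**Working it through.** **1. Does any passage close the gap?**
- 5.c.2, failure definition: it names rebound, so rebound is expected, but it does not remove or mark the specimen.
- 5.f.2: it covers stopping ARVs or a change in ARV status, not viraemia on an unchanged regimen.
- 5.f.3: it censors at superinfection only.
- 5.f.1: it concedes that OLA cannot tell selection of pre-existing mutants from new mutation. It does not separate suppressed from viraemic subjects, which plasma RNA can do.
- 5.c.2, exploratory covariates: these are transmitted resistance, timing of therapy, RNA at ARV start or initial decay, and adherence. RNA at the specimen is absent.

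So the gap stands.

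**2. The plan's own benchmark.** One of the two studies that informed the Aim 2 sample size found new mutations in 2 of 9 subjects (22%). Section 3.d says those nine had RNA below 50 throughout. Aim 2 requires only that this level be reached.

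**3. Where can rebound enter?** Entry requires suppression within the first six months, so little time is left for rebound before the 6-month specimen. The exposure is mainly at month 12.

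**4. The zero-event bound.** The exact two-sided 95% upper limit for 0 of n is 1 − 0.025^(1/n).
- n = 35: 1 − 0.025^(1/35) = 0.100. The plan's 10% is reproduced.
- n = 33, if two of the 35 had rebounded: 1 − 0.025^(1/33) = 0.106.

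With zero events rebound cannot raise the numerator. It can only leave fewer suppressed subjects behind the statement.

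**5. How many rebounds?** The pilot saw four virologic failures (5.c.2), and 83 pilot subjects started ARVs (4.g). If all four were among those 83, the share is 4/83 = 4.8%. Applied to 53 subjects this gives 53 × 0.048 = 2.6. Split in proportion to group size, 2.6 × 18/53 = 0.9 would fall among the 18 with baseline resistance. This probably overstates rebound in the eligible group, for reasons given under the objection.

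**6. Effect on the two-group difference, by assumption only.** Let s be the true rate under suppression, r the rebound rate and q the chance that a rebound yields a new mutation. The observed rate is s + (1 − s)·r·q. Take s = 10% in both groups and q = 1.
- r = 5% in both: 0.10 + 0.90 × 0.05 = 14.5% in each group, so no spurious difference.
- r = 5% without and 20% with baseline resistance: 14.5% against 0.10 + 0.90 × 0.20 = 28%.
- The same with q = 0.5: 12.3% against 19%.

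The documents give no values for r by group or for q, so these figures show a range and are not a forecast.

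**7. Cost of restricting to suppressed subjects.** With pooled proportion p̄, power = Φ{[|p₁ − p₂| − 1.96·√(p̄(1 − p̄)(1/n₁ + 1/n₂))] / √(p₁(1 − p₁)/n₁ + p₂(1 − p₂)/n₂)}, two-sided without continuity correction. For 10% against 50% with 35 and 18 subjects it is 0.89. Losing 4.8% of subjects gives 0.88, an assumed 10% gives 0.86, and an assumed 20% gives 0.82.

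**The case against.** **The main estimand is correctly labelled.** The title, objective 1, the powered test and the sentence naming the novel finding all refer to ARV therapy. This stands. A reader might infer that the primary comparison is misdefined, but it is not. The mismatch is confined to the three places that speak of suppression or success.

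**The bound cannot be inflated.** This also stands. It is tempting to call the bound fragile because 1/35 would give an upper limit of 14.9%. The plan makes the statement only for zero events, so that figure describes a claim it does not make. Only the denominator effect in step 4 remains.

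**Rebound may be rare and need not favour one group.** The four pilot failures occurred at any time in follow-up. If the protocol's failure definition was used, some may have been failures to suppress or ARV changes for delayed suppression, and the Aim 2 entry rule would exclude most such subjects. A reader might infer that rebound would concentrate in the resistant group, since 5.c.2 expects weaker suppression there, and that two such cases among 18 would add 11 percentage points. That allocation is chosen, and it needs every rebound to yield a new mutation. The pilot hazard ratios for time to suppression (4.g) were 1.1 (95% CI 0.54–2.3) and 2.3 (1.1–4.6) in subjects with low-frequency mutations, where values above 1 mean faster suppression. They show no slowing, although the first interval is wide and neither measures rebound.

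**Visit-level rules belong in an SAP, and the section 2 wording can be read as already requiring success up to the specimen.** The SAP is not shown, and its possible content is not criticised here. The point is that the protocol's stated entry and counting rule does not deliver the label placed on the result. The section 2 wording sets no operational criterion.

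**Restricting to suppressed specimens conditions on a post-baseline outcome.** This is correct, and it is why the restricted result should not replace the primary comparison.

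**Conclusion.** The point holds in a limited form. Under the rule as written, a mutation first detected after rebound on continued ARVs can be counted and then described as arising during suppression or successful therapy, mainly through the month-12 specimen. The primary comparison is sound as worded. The zero-event bound moves only slightly, from 10.0% to about 10.6% if two of 35 subjects had rebounded, a number chosen for illustration.

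The size and direction of any between-group bias cannot be determined from the protocol. Equal rebound in the two groups would raise both rates without creating a difference; unequal rebound could create one. The pilot share of about 5% rests on assuming that all four failures were among the 83 treated subjects, and probably overstates early rebound. This is worth correcting because the correction is cheap, not because a large distortion has been shown.

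**What to change.** 1. Classify each 6- and 12-month specimen by whether RNA stayed suppressed from first suppression up to that visit. State in advance which RNA criterion marks loss of suppression, since 5.c.2 uses 50 copies/mL for entry and 400 on two occasions for rebound.
2. Base the zero-event bound, and any statement about suppression or successful therapy, on suppressed specimens only.
3. Keep the all-specimen comparison as primary for objective 1, described as during ARV therapy. Show the suppressed-specimen result beside it as a descriptive companion, noting that it conditions on a post-baseline outcome.

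**Cost.** No new visits or assays are needed: Table 11 schedules RNA at every visit, and the schedule restarts at ARV start. A few specimens leave the suppression-specific estimate and its interval widens slightly. Section 5.e.2 notes that some 1996–2002 results were censored at 500 copies/mL and retested only when specimens were available. Any that remain censored cannot be classified at 50 and should be reported as such.
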